Collectively, data from these physiological outcome groups will test the central hypothesis that manual therapies—particularly spinal manipulation techniques— reduce spinal reflex gain (reflected by decreased short-latency reflex response), which in turn decreases reflexive muscle activity (i.e., spasm; reflected by diminished resting MRI T2 signal and surface EMG). The decreased muscle spasm leads to reduced pain, which should remove or reduce inhibitory effects arising from nociceptive afferents projecting to the motor cortex. This leads to an increase in motor cortex excitability (reflected by an increase in intracortical facilitation and/or decrease in intracortical inhibition). Ultimately, when pain and inhibitory input to the motor cortex are reduced, pain and disability decrease and volitional movement is improved. Additionally, the supplemental research data will test the hypothesis that male participants with chronic LBP will present with increased stiffness compared to female participants with chronic LBP, that participants with chronic LBP will present with increased stiffness compared to healthy controls, that there are no net sex effects of spinal manipulation on trunk stiffness, and both manipulative interventions will decrease passive trunk stiffness as evidenced by the trunk's initial mechanical response to multi-directional trunk perturbations.

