Passive trunk stiffness in three cardinal planes during unanticipated seated trunk perturbations will be measured in chronic LBP participants enrolled in the RELIEF study (Experiment 2) and a healthy control group (matched for gender, age, height, and weight)- recruited for the sex/gender differences supplement.

**Specific Aim 1.** To examine the effects of sex and chronic LBP on passive trunk stiffness. H1.1. Male participants with chronic LBP will present with increased stiffness compared female participants with chronic LBP. H1.2. Participants with chronic LBP will present with increased stiffness compared healthy controls.

**Specific Aim 2.** To examine sex differences in the effects of spinal manipulation on passive trunk stiffness. H2.1. There are no net sex effects of spinal manipulation on trunk stiffness. H2.2.Both manipulative interventions will decrease passive trunk stiffness as evidenced by the trunk’s initial mechanical response to multi-directional trunk perturbations.

**Specific Aim 3.** To examine the effects of sex and posture on trunk stiffness.

**Specific Aim 4.** To examine the effects of sex and trunk displacement from internally generated trunk perturbations.

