controls found LBP subjects had an 8% decrease in stiffness once they became asymptomatic.[67] However, it is unknown if an increase in stiffness at one or more vertebral segments translates to an increase in stiffness in the lumbar spine as a whole. Yet this would be completely consistent with the clinical perspective that manipulative therapies are aimed at reducing stiffness of individual segments (and possibly the trunk as a whole), with the goal of decreasing pain and improving function. While Gombatto and colleagues found an increase in trunk stiffness in participants with mechanical LBP, it is worth noting that trunk stiffness was determined from the slope of the force-displacement curve in a quasi-static condition. Thus static and not dynamic trunk stiffness was assessed in this cohort.[79] However, Hodges and colleagues have recently suggested that an increase in dynamic trunk stiffness occurs in subjects with recurrent LBP and may, in part, account for the recurrence of LBP symptoms. But this assessment was on asymptomatic participants (i.e., currently pain free, but a history of recurrent LBP) and was restricted to the sagittal plane. While trunk stiffness has also been assessed in numerous movement tasks in healthy individuals,[70-72] no published studies have examined the influence of a course of manipulative therapies on trunk stiffness. While there is recent evidence that sagittal plane trunk stiffness is greater in men compared to women, this has been only assessed in a paradigm that required active trunk co-contraction.[65] This is due, in part, to the use of a system that required a rigid linkage between the actuator and the trunk to assess trunk stiffness. The additional mass of the rigid link system reduces the sensitivity of the system to detect dynamic stiffness in a resting state. A significant advantage of our system to assess trunk stiffness is that light weight non-deformable Kevlar cables are used in place of a rigid linkage (see Figure 2A). This allows the subject to be released following a perturbation so that the actuator system is not part of their response, thereby enabling sex differences in dynamic trunk stiffness to be assessed with greater sensitivity. Further, trunk stiffness in the axial and coronal planes has not been examined in patients with chronic LBP. Interestingly, recent data suggests that males have greater sagittal-plane trunk stiffness compared to females,[65] but females have a higher prevalence of LBP. Thus an underlying mechanism of LBP may be different in males and females, or it could be due to the limitations of the system used to assess trunk stiffness. Accordingly, the proposed aims provide a robust method to determine the effects of sex and spinal manipulative therapies on trunk stiffness in response to multi-directional seated perturbations.

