result in a small trunk angular displacement (5-10 degrees) and a long latency postural reflex response of the trunk muscles. In this paradigm, the participant will be exposed to 3 loads in each of the 6 directions listed above. The sequence of the load direction (e.g. flexion, extension, rotation right etc.) will be randomized for each participant.

Once data are collected, system properties of the trunk will be estimated from the time of onset of the perturbing forces until maximal trunk displacement. Effective trunk mass (M), damping (B), and stiffness (K) will be assumed to be constant after the perturbation and will be described by a second-order linear model (Equation 1).

$$F(t) = M * \text{Acceleration}(t) + B * \text{Velocity}(t) + K * \text{Position}(t)$$

$F(t)$  is the resultant force vector on the trunk. The change in trunk position will be measured using the Vicon system. Trunk velocity and acceleration will be determined using a Savitzky-Golay filter. [80] The force applied to the trunk during the perturbation will be measured from the pairs of load cells that are in-series with the actuators. Consistent with the methods proposed by Hodges and colleagues, M, B, and K will be assumed to be constant, and a standard least squares procedure will be used to solve the estimation. The data for the second order linear equation will be integrated numerically twice over time to increase the

[figure not shown]

procedure's robustness.

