### Assessing Trunk Displacement Using Internally Generated Trunk Perturbations

To assess the effects of sex on trunk displacement with internally generated perturbations, participants will be asked to perform the following 3 rapid (duration of 100 ms) voluntary movements while in a standing posture: 1) flex both shoulders 90° to create a trunk flexion perturbation, 2) abduct the left shoulder 90° to create a trunk side-bending left perturbation, and 3) flex the right shoulder 90° while simultaneously extending the left shoulder 90° to generate a trunk rotation left perturbation. The participants will 6 trials of each of these tasks performed in a random order. To normalize the magnitude of the internally generated force, participants will perform the rapid shoulder movements with weights equal to 5% of body mass. Thus a participant weighing 120 lbs will hold a total of 6 lbs of weight to compete the task. The primary dependent measure is trunk displacement in the three-cardinal planes.

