## Exclusion criteria

Participants must not have any of the following exclusion criteria to participate in this study:

- Have a personal history of the following neurological disorders: Alzheimer's, Amyotrophic Lateral Sclerosis, Multiple Sclerosis, Parkinson's, or Stroke.
- Have a personal history of the following cardiorespiratory disorders: Congestive heart failure, Heart attack in past 24 months.
- Have a personal history of the following musculoskeletal disorders: Rheumatoid Arthritis, pathologic fractures of the spine, avascular necrosis or osteonecrosis, severe osteoarthritis. Including a history of spine surgery or a hip arthroplasty.
- Have active cancer.
- Be Blind.
- Have used narcotics or muscle relaxants within 30 days prior to study enrollment.
- Report being pregnant.
- Have a body mass index greater than 35 kg/m^2.
- Have clinical depression (i.e., subjects who score 24 or higher on the Center for Epidemiology Depression Scale).
- Current drug or alcohol use or dependence that, in the opinion of the PIs, would interfere with adherence to study requirements

## Hypothesis Testing: Aim 1

Hypothesis 1.1. Male participants with chronic LBP will present with increased stiffness compared female participants with chronic LBP

Hypothesis 1.2. Participants with chronic LBP will present with increased stiffness compared healthy controls.

Separate 2 Group (Chronic LBP, Matched Healthy Control) x 2 Sex (Male, Female) mixed-model MANOVAs will be conducted on trunk stiffness measures.

## Hypothesis Testing: Aim 2

Hypothesis 2.1. There are no net sex effects of spinal manipulation on trunk stiffness.

Hypothesis 2.2. Both manipulative interventions will decrease passive trunk stiffness as evidenced by the trunk's initial mechanical response to multi-directional trunk perturbations.

Separate 3 Group (Manipulation, Mobilization, Sham Laser) x 2 Gender (Male, Female) x 3 Time (Baseline, Immediately following initial treatment, 48 hrs post-3 weeks of treatment) mixed-model MANOVAs will be conducted on trunk stiffness measures.

**Specific Aim 3.** To examine the effects of sex and posture on trunk stiffness.

**Hypothesis 3.1.** Healthy Male participants will present with increased trunk stiffness compared to healthy female participants.

**Hypothesis 3.2.** Trunk stiffness will be greater in sitting compared to standing.

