Separate 2 Sex (Male, Female) x 2 Posture (Male, Female) mixed-model MANOVAs will be conducted on trunk stiffness measures.

**Specific Aim 4.** To examine the effects of sex and trunk displacement from internally generated trunk perturbations.

**Hypothesis 4.1.** Healthy Male participants will present with less trunk displacement during internally generated trunk perturbations compared to healthy female participants.

Separate 2 Sex (Male, Female) mixed-model MANOVAs will be conducted on trunk displacements.

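### The two between-sex comparisons of trunk stiffness (H1.1 and H3.1) use stiffness unadjusted for body size, so a significant result could reflect larger bodies rather than a sex-specific trunk property

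*Supplement*

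**What the plan says.** Section 1.1 (Mechanistic Component) and the appendix state H1.1: "male participants with chronic LBP will present with increased stiffness compared to female participants with chronic LBP". In the appendix, H3.1 reads: "Healthy Male participants will present with increased trunk stiffness compared to healthy female participants". Neither mentions body size.

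The measure is defined in the appendix under Assessing Trunk Stiffness. Force is modelled as M times acceleration plus B times velocity plus K times position, and "Effective trunk mass (M), damping (B), and stiffness (K) will be assumed to be constant after the perturbation". The three constants are solved by least squares. No division of K by mass, height or a trunk dimension is described.

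The tests are in the appendix hypothesis-testing text. Aim 1: "Separate 2 Group (Chronic LBP, Matched Healthy Control) x 2 Sex (Male, Female) mixed-model MANOVAs will be conducted on trunk stiffness measures". Aim 3: "Separate 2 Sex (Male, Female) x 2 Posture (Male, Female) mixed-model MANOVAs will be conducted on trunk stiffness measures" (the posture levels are evidently misprinted for sitting and standing). No covariates are listed for either.

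Body size is handled in three other places:
- Controls are "matched for gender, age, height, and weight" to the Experiment 2 patients (appendix, Specific Aims).
- The perturbing force is set from anthropometrics (section 6.2.2 and the appendix).
- For Aim 4: "To normalize the magnitude of the internally generated force, participants will perform the rapid shoulder movements with weights equal to 5% of body mass".

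**The concern.** The plan treats size as relevant when it chooses controls, when it sets the perturbing force and when it sets the Aim 4 hand weights. It does not do so when it compares men's K with women's K.

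In the plan's own model, two trunks with the same dynamic behaviour but different mass have K in proportion to mass. If men in the sample are larger, some or all of a male-female difference in K may be due to size.

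The appendix rationale starts from the observation that men have stiffer trunks while women have more back pain, and comments: "Thus an underlying mechanism of LBP may be different in males and females". It goes on to offer limitations of the measuring system as the alternative. Body size is not among the explanations considered. A significant sex effect on unadjusted K could then be read as a sex-specific trunk property when it is not one.

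**Working it through.** **1. Do other provisions already deal with size in the sex contrast?**

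- *Matching.* Each control has the same sex as the matched patient. This balances size between patients and controls within each sex and leaves men against women untouched.
- *Force scaling.* The model is linear. Multiplying the force by a constant multiplies position, velocity and acceleration by the same constant, so K does not change. A numerical fit with M = 30, B = 200 and K = 3000 returned K = 3000 both at the base force and at 1.4 times that force.
- *Separate estimation of M.* M comes from the same fit, but no listed test uses it.
- *Covariate rule in section 9.5.* It is triggered by differences between the three treatment arms, not between the sexes. Section 9.5 also sends the supplement's analysis to the appendix, which has no such rule.

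**2. Is there a figure in the plan to reproduce?** Not for this point. The only power figure for the sex analysis (0.85, N = 120) is for the sex-by-group interaction. It does not bear on whether body size explains a sex main effect.

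**3. How often would size alone give a significant sex effect?**

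From the appendix (Number of Subjects and Power): 27 men, 33 women, p < 0.05.

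Assumed, because the documents give none of these:
- a two-sided test;
- men heavier than women by a ratio r = 1.2 (range 1.1 to 1.3);
- within-sex CV of K = 0.30 (range 0.20 to 0.40);
- K proportional to mass to the power b, with b from 0.33 to 1;
- no sex effect on K beyond size.

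The calculation is a two-sample t-test on one stiffness measure, standing in for the planned MANOVA on several.

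Let q = r^b. Then d = (q - 1) / (CV x (q + 1)/2). The noncentrality is d / sqrt(1/27 + 1/33) = d / 0.2595, with 58 degrees of freedom.

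| b | q | d | noncentrality | probability of p < 0.05 |
|---|---|---|---|---|
| 1 | 1.200 | 0.200/(0.30 x 1.100) = 0.61 | 2.34 | 0.63 |
| 0.67 | 1.130 | 0.130/(0.30 x 1.065) = 0.41 | 1.57 | 0.34 |
| 0.5 | 1.095 | 0.095/(0.30 x 1.048) = 0.30 | 1.17 | 0.21 |
| 0.33 | 1.062 | 0.062/(0.30 x 1.031) = 0.20 | 0.77 | 0.12 |

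These compare with 0.05 if size had no influence.

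**4. Range.**
- With b = 1, the grid r = 1.1 to 1.3 and CV = 0.20 to 0.40 gives 0.15 to above 0.99.
- With b = 0.33, the same grid gives 0.06 (r = 1.1, CV = 0.40, d = 0.08) to 0.37 (r = 1.3, CV = 0.20, d = 0.43).
- If H1.1 were read from the sex main effect over patients and controls together (54 men, 66 women), the divisor is sqrt(1/54 + 1/66) = 0.1835. At r = 1.2 and CV = 0.30 the probability is then 0.91 for b = 1 (noncentrality 3.30) and 0.19 for b = 0.33 (noncentrality 1.09).

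**5. Does adjustment separate the two explanations?** A simulation (3,000 runs per setting, 27 v 33) took K proportional to mass, men 15 to 25% heavier and residual SD of log K of 0.2 to 0.3. The unadjusted sex test rejected in 36 to 92% of runs. With log body mass as a covariate it rejected in 4.5 to 5.9%, about the nominal 5%.

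**The case against.** The strongest reply is that the hypotheses as worded are descriptive: men will have stiffer trunks. An unadjusted contrast answers that validly. Size is partly a consequence of sex, so adjusting for it changes the question from the total effect of sex to a direct effect. This stands, and it is why the planned contrast should stay.

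A reader might also infer that larger male bodies will by themselves confirm the sex hypothesis. The documents do not support that. They give no body sizes, no SD of K and no relation of K to mass. Under weaker-than-proportional scaling the probability falls to between 0.12 and 0.34 at the central inputs.

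A reader might infer, too, that the supplement as a whole is undermined. It is not:
- H1.2 compares patients with size-matched controls.
- The powered sex-by-group interaction has size balanced across groups within each sex.
- Aim 2 concerns change within randomised participants.

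Finally, the plan does not state the units in which stiffness will be reported. The stiffness models were still to be developed, and the fit follows a cited method that is not shown. The contents list a caveats section for Aims 1 and 2 whose text does not appear in the appendix shown. Some size handling may therefore have been intended, but nothing in the text commits to it.

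**Conclusion.** The concern holds for the two between-sex main effects, H1.1 and H3.1, and only for them. As written, the plan cannot tell whether a significant difference in K comes from larger bodies or from a sex-specific property of the trunk. At men 20% heavier, CV 30% and 27 v 33, size alone would give a significant result with probability about 0.1 to 0.6 as the scaling exponent goes from 0.33 to 1. Those inputs are assumptions, and the exponent matters most. The gap in the text does not depend on them. The planned test remains valid for the descriptive hypothesis. What lacks support is an interpretation that goes beyond body size.

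**What to change.** In the appendix hypothesis-testing section, for Aims 1 and 3:

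- Keep the planned contrasts on unadjusted K as the tests of H1.1 and H3.1.
- Pre-specify one additional analysis of each, with body mass and height as covariates, reported beside the planned one. Naming a single method avoids leaving a choice between covariates and a ratio such as K/M, whose two parts come from the same fit.
- State that a sex difference in trunk mechanics beyond body size will be claimed only if the adjusted contrast supports it.

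The cost is about two sentences and one extra model per hypothesis. No new measurement is needed: the Visit 1 physical exam form records patients' height and weight, and matching requires both for controls. The downsides are some loss of precision, because size and sex are correlated, and an adjusted estimate that must be described as a direct rather than a total effect of sex.

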## **1.2 RCT Component**

The primary objective of this component is to determine whether individuals with chronic low back pain have greater reductions in disability and pain following one of the following interventions delivered for 3-weeks: 1) spinal manipulation, 2) spinal mobilization, or 3) sham Laser. Hypothesis: The manual therapy interventions will result in a 2 point greater reduction in pain and a 3 point greater reduction in disability when compared to the sham Laser intervention, with the spinal manipulation intervention demonstrating the greatest reduction in pain and disability of all three treatment interventions.

## 2. BACKGROUND AND RATIONALE

### 2.1 Background on Low Back Pain and Manual Therapy Treatments

Low back pain is one of the most common reasons for seeking medical care and accounts for over 3.7 million physician visits/year in the U.S. alone. Ninety percent of adults will experience low back pain in their lifetime, 50% will experience recurrent LBP, and 10% will develop chronic pain and related disability.[1-4] According to a recent national survey, more than 18 million Americans over the age of 18 years received manipulative therapies in 2007 at a total annual out of pocket cost of \$3.9 billion.[5] Spinal manipulative treatments can be broadly classified as manipulation-based or mobilization-based techniques. Manipulation-based techniques (e.g., translatory thrust) apply a high-velocity, low-amplitude force to the spine and are often accompanied by an audible sound from one or more joints. In contrast, mobilization-based techniques (e.g., muscle energy) use a low-velocity, low-force approach that generally does not produce audible joint sounds. Recent evidence suggests that there are differences in the short-term clinical effects of manipulation-based versus mobilization-based spinal techniques.[6] Specifically, manipulation-based techniques result in greater reduction in pain and disability compared to mobilization-based techniques. While there is growing evidence for the clinical effectiveness of manipulative therapies to treat low back pain, little is known on the neurophysiologic consequences and effects of either manipulation-based or mobilization-based treatments.[7-11] Further, additional data is needed to understand how these different manual therapy techniques effect clinical changes in pain and disability. The lack of empirical data hinders acceptance by the wider scientific and health-care communities, and it also limits the development of rational strategies for using manipulative therapies.

### 2.2 Study Rationale

Background & Significance: Over the past decade there has been growing scientific evidence supporting the clinical effectiveness of manual therapy treatments for low back pain.[10-17] However, little scientific evidence has been offered to explain the effects and mechanisms underlying these treatments. Many scientists and clinicians have long postulated that spinal manipulation exerts its biologic effects on segmental components of the central nervous system.[18-33] It has been proposed that manual therapies act through a cascade of neurophysiologic responses [26, 34] to reduce muscle spasm and subsequent pain. Two general models of low back pain that have received the most attention (i.e., pain adaptation and pain-spasm-pain models) have been used to support these propositions.

The pain adaptation model posits a decrease in trunk agonist muscle activity and an increase in antagonist muscle activity that serves a protective function.[35] This model also predicts no difference in resting activity of the trunk muscles. In contrast, the pain-spasm-pain model of LBP (Figure 1) suggests that pain leads to muscular hyperactivity (spasm), which in turn causes pain.[36] While two distinct neural pathways have been proposed to support this model, the common theme is that increased excitatory input to the alpha-motoneuron pool leads to more sustained and intense muscle activity in LBP patients (for review see Van Dieën et al., 2003) [37]. Spinal manipulation has been proposed to act via the pain-spasm-pain model, yet this has not been clearly demonstrated.

We recently reported that a single session of spinal manual therapy treatment—involving a combination of manipulation and mobilization techniques—determined by imaging [18]. Consistent with these findings, a few studies [38-41] noted reduced paraspinal muscle activity, as determined by surface electromyography, following spinal manipulation on individuals with low back pain. Further, our preliminary data also indicate that the amplitude of short-latency stretch reflexes, but only if an audible joint sound is produced [43]. While manipulative treatments could act via the pain-spasm-pain model by reducing the underlying segment),[40, 42, 44-48] there are three primary limitations to these studies that make such conclusions have:

- Not taken a comprehensive approach to determine the effects of manipulation on components of the central nervous system (cortical and spinal) that could explain the reported reductions in muscle activity. Thus, the neurophysiologic mechanisms underlying spinal manipulative treatments remain largely unknown.
- Primarily focused on manipulation-based treatments and disregarded mobilization-based treatments. Thus, the physiologic effects of manipulation-based versus mobilization-based treatments are unknown.
- Not examined both the immediate physiologic effects, those following a course of treatment, as well the sustained effects (i.e., changes lasting after treatment has concluded).

[figure not shown]

**Figure 1.** Two neural pathways suggested to form the basis of a pain-spasm-pain cycle. Left side: Nociceptive afferents (N) transmit feedback via excitatory interneurons (E) to the alpha motor neurons ( $\alpha$ ) that cause increased muscle activation (spasm). Right side: Nociceptive afferents (N) provide excitatory input on the gamma motor neurons ( $\gamma$ ) that increase the sensitivity of the muscle spindles (s), which activate alpha motoneurons via excitatory interneurons (E) further increasing muscle activation and pain.

From Van Dieën et al., *J Electromyography Kinesiol*, 2003.

The RELIEF Study will address all of these shortcomings. The Mechanistic Component will assess treatment-induced changes at the muscular, spinal, and cortical levels. Importantly, the RCT Component of the RELIEF Study will provide critical data on treatment effectiveness, which will also allow the examination of the relationship between the changes in the physiological outcomes and clinical outcomes on symptom resolution following treatment.

Known and Potential Risks of the Treatment Interventions: Spinal manual therapies are some of the most common treatments for low back pain, and the risk of serious injury from the lumbar spinal manual therapy techniques is reported to be extremely small [49]. Gouveia recently conducted a systematic review to examine the adverse reactions associated with manual therapies. Their search identified 46 articles that included data concerning adverse events. With regards to lumbar (i.e., not cervical) manipulation, most of the adverse events reported were benign and transitory [49]. They did however report some cases of serious adverse events, such as disc herniation and progression to cauda equina syndrome [49]. However, others have estimated of the incidence of serious adverse events from published case reports and case series to be extremely rare (i.e., about 1 case event per 1 to 2 million treatments) [50]. A more common risk is soreness, which generally dissipates within hours to days.

Rationale regarding the supplemental research is included in the Appendix.

